### Trial design

2.2

This is an outcome assessor- and data analyst-blinded, partial randomized controlled trial conducted at the Second Affiliated Hospital of Heilongjiang University of Chinese Medicine from January 1, 2021 to December 31, 2023. A total of 80 subjects who met the inclusion criteria including 25 healthy volunteers, 25 T2DM patients with normal cognitive function, and 30 patients with VCI combined with T2DM were recruited into the study. First, they were scanned by fMRI, through the calculation and analysis of VBM indexes, the changes in hippocampal volume and function in the 3 groups of patients were compared to determine the difference between type 2 diabetes patients and healthy volunteers, correlation between hippocampal structural and functional changes in patients with normal cognitive T2DM and VCI patients with T2DM. Then, 30 VCI patients with T2DM were randomly divided into the experimental group and the control group, the control group was given routine drug therapy to control blood glucose and improve cognitive function, the experimental group was given acupuncture-rehabilitation therapy on the basis of the control group. The primary outcomes were obtained by VBM calculation and serum biomarkers (SOD, MDA, BDNF) detection, and the secondary outcome indexes were assessed by neuropsychological scales such as Montreal Cognitive Assessment (MoCA), Wechsler Memory Scale IV edition (WMS-IV), FIM, among others. Serum biological indicators and neuropsychological scale will be conducted before treatment, as well as 4 weeks, 8 weeks, and 12 weeks after treatment respectively, fMRI scan will be conducted before treatment and 12 weeks after treatment respectively, to observe the intervention effect of acupuncture-rehabilitation therapy on cognitive function of VCI patients with T2DM. Figure 1 and Table 1*present the technology roadmap and clinical observation flow charts, respectively.*

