#### Imaging criteria

2.8.1

Neuroimaging tests need to meet the minimum imaging criteria for the diagnosis of VCI by VASCOG, that is, at least one of the following imaging findings: one large vessel cerebral infarction is sufficient to cause VaMCI, whereas the diagnosis of severe VCI usually requires two or more large vessel cerebral infarct; the presence of an extensive or critical cerebral infarction in the thalamus or basal ganglia region may be sufficient to cause severe VCI; there were >2 luminal infarcts outside the brain stem (The luminal infarction of 1 to 2 key parts or 1 to 2 non-key parts combined with extensive white matter hyperintensity); extensive or fused white matter high signal; cerebral hemorrhage in key areas, or ≥2 cerebral hemorrhage; . a combination of the above forms.

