#### Inclusion criteria of VCI patients with T2DM

2.9.1

1.It conforms to the diagnostic points of T2DM and VCI, and has been confirmed to have suffered from ischemic or hemorrhagic stroke by CT or MRI.2.With cognitive impairment, the score of the Montreal Cognitive Assessment scale (MoCA-Beijing version) is <26 (if the length of education is <12 years, one point is added to the test results to correct the cultural influence). The overall cognitive function is fully preserved, and the score of Mini Mental State scale (MMSE) ≥24. It did not meet the diagnostic criteria of dementia in the fourth edition of the American Diagnostic and Statistical Manual of Mental Disorders, with a clinical dementia scale (CDR) score of 0.5. Activities of daily living (ADL) were not significantly impaired, and the IADL score ≥16.3.Can cooperate to complete fMRI scan.4.The course of stroke ranges from 3 to 12 months.5.The range of age from 50 to 60 years old, right-handedness.6.No verbal language dysfunction.7.Have not received acupuncture or rehabilitation treatment in the past three months.8.Not accompanied by depression, mental symptoms and infectious diseases.9.The following categories of drugs were not used within 30 days before screening for cognitive impairment: drugs for the treatment of Alzheimer disease or dementia, anti-Parkinson disease drugs, short-acting antianxiety agents, nerve sedatives or analgesics, antiepileptic drugs, hormones, drugs with significant cholinergic or anticholinergic side effects.

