### Inclusion criteria for patients with normal cognitive function in T2DM

2.10

1.Meet the diagnostic criteria of T2DM, and was confirmed by CT or MRI to exclude stroke.2.Cognitive function is normal, MoCA score ≥26 points (if the length of education is <12 years, one point is added to the test results to correct the cultural influence). MMSE score ≥24.CDR score is 0.IADL score ≥16.3.Can cooperate to complete fMRI scan.4.The range of age from 50 to 60 years’ old, right-handedness.5.No verbal language dysfunction.6.Have not received acupuncture or rehabilitation treatment in the past 3 months.7.Not accompanied by depression, mental symptoms, and infectious diseases.8.The following categories of drugs were not used within 30 days before screening for cognitive impairment: drugs for the treatment of Alzheimer disease or dementia, anti-Parkinson disease drugs, short-acting antianxiety agents, nerve sedatives or analgesics, antiepileptic drugs, hormones, drugs with significant cholinergic or anticholinergic side effects.

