### Inclusion criteria of healthy volunteers

2.11

1.Do not meet the diagnostic criteria for diabetes, and stroke is excluded as confirmed by CT or MRI.2.Cognitive function is normal, MoCA score ≥26 points (if the length of education is <12 years, 1 point is added to the test results to correct the cultural influence). MMSE score ≥24.CDR score is 0.IADL score ≥16.3.Can cooperate to complete fMRI scan.4.The range of age from 50 to 60 years’ old, right-handedness.5.Diseases without brain trauma, drug and alcohol dependence that may affect the structure and function of the brain, not accompanied by depression, mental symptoms and other diseases.

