### Primary outcome measurement

2.23

**VBM:** The VBM is an automatic, comprehensive and objective analysis technique for magnetic resonance imaging (MRI) of brain structures based on voxels. VBM can be noninvasively and accurately study the morphology of living brain and reflect the difference of corresponding anatomical structure by analyzing the changes of each voxel. It is a reliable method to evaluate gray and white matter lesions and plays an important role in the diagnosis of diseases related to cognitive impairment.

**SOD:** The SOD is an active substance derived from living organisms, which can eliminate harmful substances produced by living organisms during metabolism. SOD is mainly used to prevent and treat local cerebral hemorrhage, ulcers, eliminate inflammation, arrhythmia, rheumatism, rheumatoid disease, radiation injury, drug poisoning, and other diseases, and can prevent and treat brain function recognition disorders caused by specific or non-specific brain damage.

**MDA:** The MDA is the final product of lipid peroxide metabolism formed by oxygen free radicals attacking unsaturated fatty acids in biological membranes. It is cytotoxic and can cause cross-linking reactions of DNA, membrane proteins, enzymes, among others, and increase membrane permeability, resulting in changes in the structure, function and metabolism of cell membranes result in damage or death of cells and even the body, which can directly reflect the intensity and rate of lipid peroxidation in the body, and indirectly reflect the content of oxygen free radicals and the degree of nerve cell damage. It is an important biomarker reflecting lipid peroxidation and oxidative stress.

**BDNF:** The BDNF is a protein with neurotrophic effect. It is one of the very important members of neurotrophin family. It was first found in pig brain by Barde et al. Because it can promote the growth, reproduction, regeneration and repair of injured neurons, it mainly has extensive neuroprotective and neurotrophic effects, also is important for neuron survival, maintenance of normal function, and repair after damage. Therefore, it is mainly expressed in the central nervous system, especially in the cortex and hippocampus.

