#### Statistical processing and result presentation of brain function data

2.29.2

Statistical analysis is carried out by using DPASFA, SPM12, Xjview, Rest, and other software based on MATLAB platform.

The values of VBM, ReHo, and FC of healthy volunteers, T2DM cognitive normal group, and VCI group with T2DM were analyzed by ANOVA, with sex, age and years of education as covariates. The test level was set to: cluster level *P* < .05 (FWE or FDR correction). If *P* < .05 and could at least pass the FDR correction, there was a significant difference between the 2 groups of patients and healthy volunteers, which was statistically significant.

In the VCI group with T2DM, the data of VBM, ReHo, and FC in the experimental group and the control group were compared by double-sample *t* test. Paired-sample *t* test was used for intra-group comparison between the 2 groups before and after treatment. The test level was set as: cluster level *P* < .05 (FWE or FDR correction). If *P* < .05 and could at least pass the FDR correction, it was considered that there was a significant difference between the experimental group and the control group, which was statistically significant.

The statistical results were presented by Xjview and Mricron software.

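### The VBM tests fixed in section 2.29.2 make no stated allowance for stroke lesions, which confounds the three-group contrast and leaves the small randomised contrast noisy

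*Protocol article*

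**What the plan says.** - Section 2.2 (Trial design) makes VBM co-primary with three serum markers: "The primary outcomes were obtained by VBM calculation and serum biomarkers (SOD, MDA, BDNF) detection". Section 2.1 gives hippocampal volume and function as the imaging target.
- Section 2.9.1 requires that each VCI patient "has been confirmed to have suffered from ischemic or hemorrhagic stroke by CT or MRI", and adds: "The course of stroke ranges from 3 to 12 months". The imaging criteria in section 2.8.1 admit sizeable lesions, for example "one large vessel cerebral infarction is sufficient to cause VaMCI", and also deep infarcts, haemorrhage and extensive white-matter change.
- Both comparison groups are the opposite by design. For T2DM with normal cognition, section 2.10 requires that the diagnosis "was confirmed by CT or MRI to exclude stroke". For healthy volunteers, section 2.11 says "stroke is excluded as confirmed by CT or MRI".
- Section 2.29.2 fixes three VBM analyses: a three-group ANOVA with sex, age and years of education as covariates; a between-arm comparison in which "the data of VBM, ReHo, and FC in the experimental group and the control group were compared by double-sample" t test, with no covariate named; and paired t tests within each arm.
- Section 2.23 says of VBM: "It is a reliable method to evaluate gray and white matter lesions". No section mentions lesion site, lesion volume or masking. No section describes VBM preprocessing of any kind.

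**The concern.** VBM assigns each voxel to a tissue class and warps each brain to a common template. Infarcted or haemorrhagic tissue can be misclassified and can disturb the warp around it, so a lesion may appear as missing grey matter. The three analyses suffer differently.

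- **Three-group ANOVA.** Stroke is present in all 30 VCI patients and in none of the 50 comparison subjects. A deficit in the VCI group may be the lesion and not atrophy linked to cognitive impairment. This is systematic.
- **Paired tests within arms.** Any natural change in the lesion over 12 weeks enters the before-after difference and can be taken for a treatment effect.
- **Randomised comparison.** Lesions add variance and chance imbalance at 15 per arm. This costs power and clouds interpretation, but it is not systematic bias.

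The error would also spread: section 2.29.3 correlates the significant brain regions with scales and serum markers, so a cluster shaped by lesions would carry into the mechanistic claims.

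**Working it through.** The plan gives no VBM figure to reproduce; its sample size (13 per group, 15 after dropout) rests on MoCA. The document also gives no lesion frequency or size, so the lesion inputs below are assumptions, shown as ranges.

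**Inputs from the protocol:** 15 patients per randomised arm, 30 VCI patients, 25 per comparison group, test level 0.05.

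**Assumptions:** a share *p* of VCI patients has a lesion that lowers a regional volume by *b* SD. Otherwise the volume has SD 1 and there is no group difference. These are single-region t tests. They do not imitate the cluster-level correction or the covariate-adjusted ANOVA, so they show direction and order of size only.

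**1. VCI (30) against a stroke-free group (25), no true difference beyond the lesion effect.** The expected false difference is *b·p*. Its standard error is √[(1 + b²p(1−p))/30 + 1/25].
- p = 0.1, b = 1: 0.10 / √(1.09/30 + 1/25) = 0.10 / 0.276 = 0.36 standard errors. Simulated false rejection: 6%.
- p = 0.3, b = 2: 0.60 / √(1.84/30 + 1/25) = 0.60 / 0.318 = 1.88 standard errors. Simulated: 43%.
- p = 0.5, b = 2: 1.00 / √(2/30 + 1/25) = 1.00 / 0.327 = 3.06 standard errors. Simulated: 84%.

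**2. Randomised arms, 15 per arm.** Lesions are independent of arm, so the expected false difference is zero. Simulated type I error (20,000 runs per setting) was 4.7% to 5.2%. The cost is variance, which becomes 1 + b²p(1−p), so a true 1 SD effect shrinks to 1/√(1 + b²p(1−p)).
- No lesion effect: effect 1.00, power 75%.
- p = 0.1, b = 1: variance 1.09, effect 0.96, power 72%.
- p = 0.3, b = 2: variance 1.84, effect 0.74, power 49%.
- p = 0.5, b = 2: variance 2.00, effect 0.71, power 46%.

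**3. Chance imbalance at 15 per arm.** With X and Y independent Binomial(15, p), P(|X − Y| ≥ 3) is 0.249 at p = 0.2, 0.318 at p = 0.3 and 0.362 at p = 0.5. If exactly 9 of the 30 are affected, the hypergeometric figure is 0.43. For a continuous covariate such as lesion volume, the standardised arm difference has SD √(2/15) = 0.365, so it exceeds 0.5 SD in about 17% of randomisations.

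**4. Paired tests.** The documents give no rate of lesion change, so no figure is possible. The point is structural: a paired test in one arm has no comparator with which to separate treatment from the natural course.

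**The case against.** - **A reader might infer that VBM will be run without lesion masking.** The documents do not say so. The article describes no segmentation, normalisation or smoothing, its software list is open-ended, and section 2.28 leaves a statistical analysis plan to a third party. Such detail is commonly left to that plan. What stands is that section 2.29.2 does fix the tests and does list covariates for one of them, and nothing about the lesion appears in either.
- **A reader might infer that the between-arm result would show lesions instead of treatment.** Randomisation rules this out as systematic bias. Lesion site, size and natural course are independent of arm, and chance imbalance is variation that the t test already allows for. The head-count figures in step 3 therefore do not measure bias. The loss of power stands, as does the harder interpretation of any one observed difference.
- **The lesion burden may be modest.** Section 2.9.1 restricts entry to patients without dementia (MMSE at least 24, CDR 0.5), section 2.8.1 does not name the hippocampus, and section 2.12 excludes other focal injury affecting cognition, though its scope is unclear. This is fair, and it is why the size is a range that starts near zero. It does not remove the design fact that stroke separates the VCI group completely from both comparison groups.
- **The remark in section 2.23 is general.** It describes VBM and is not a plan for handling infarcts. Agreed; the point does not rest on it.

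**Conclusion.** The point holds in this form: the VBM analyses stated in section 2.29.2 make no allowance for lesions that one group has by definition and the other two cannot have. The main harm is to the three-group ANOVA, where false rejection ran from 6% to 84% across the assumed settings. The within-arm tests cannot separate treatment from natural lesion change. The randomised test keeps its type I error but loses power, from 75% to between 72% and 46% for a true 1 SD effect, and is open to chance lesion imbalance. All sizes rest on assumed lesion shares and shifts in a single-region model. The direction of each effect follows from the entry criteria and the stated tests alone. The plan should be changed, because the remedy is cheap and needs no new data.

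**What to change.** In section 2.29.2, state that:

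1. A lesion mask is made for each VCI patient from the baseline structural scan, either automatically or drawn blind to arm. It is used in segmentation and normalisation, and lesioned voxels are excluded from the three-group and between-arm VBM comparisons.
2. The between-arm two-sample t test is replaced by a model with baseline lesion volume and the baseline VBM value as covariates.
3. The unmasked, unadjusted analysis is reported as a sensitivity analysis, and within-arm change is not read as a treatment effect.

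Keep left and right hippocampus separate. Do not substitute the unaffected side for the affected one, because the Introduction gives the two sides different functions and the outcome would then mix different quantities.

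Masking is the remedy for the three-group contrast. Lesion volume cannot serve as a covariate there, since it is zero by design in both comparison groups. Effects of the stroke away from the lesion would remain, and the report should say so.

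Cost: wording, and image-processing time for about 30 patients on scans already scheduled. Brain coverage will be slightly smaller. No extra patients or scans are needed.

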### Sample size

2.5

We will conduct this study using a partial randomized controlled trial design, and the main observed outcome will be improvements in VCI patients with T2DM cognitive function. Our previous clinical observation found that 4 weeks of acupuncture-rehabilitation therapy treatment and routine drug therapy can improve scores on the MoCA scale by 3.13 ± 0.75 and 1.53 ± 0.33 points, respectively.^[5]^ Use PASS15.0 software to calculate, with the significance test level set at 0.05 and the test power at 0.9, the required sample size was 13 subjects for each group. Considering a dropout rate of 15%, a total of 30 subjects needed to be enrolled in VCI group with T2DM (15 participants per group). Then the Healthy volunteers group and T2DM group with normal cognitive function group were matched with the corresponding patient volume (25 participants per group). Therefore, a total of 80 subjects were included in this study.

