#### Statistical analysis of general data, behavioral tests, and blood biomarkers

2.29.1

The metrological data of the measured data were expressed as “mean ± standard deviation,” and the normality test was carried out. If all data were in line with normal distribution (*P* > .05), *χ*^2^ test was used for counting data, *t* test was used for measurement data, double-sample *t* test was used for comparison between the 2 groups, and paired-sample *t* test was used for comparison within the group. The test level was *P* = .05, if *P* < .05 indicated statistically significant difference. The above statistical work is analyzed and processed by specialized statisticians using SPSS25.0 statistical software (SPSS Inc, Chicago, IL).

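### The arm comparison omits a baseline term although every outcome has a pre-treatment value, and the imaging decision rule does not say which P value it uses

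*Protocol article*

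**What the plan says.** Section 2.29.2 (brain function data) states for the randomised VCI patients that "the data of VBM, ReHo, and FC in the experimental group and the control group were compared by double-sample" t test. It then adds a paired t test before and after treatment within each arm and sets one cluster-level threshold of P < .05 with FWE or FDR correction. If P < .05 and at least the FDR correction is passed, "it was considered that there was a significant difference between the experimental group and the control group, which was statistically significant". The sentence does not say which of the two tests supplies that P.

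Section 2.29.1 (general data, behavioural tests, blood biomarkers) has the same pair of tests: a double-sample t "test was used for comparison between the 2 groups, and paired-sample" t test within the group.

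Covariates (sex, age, years of education) are named only for the non-randomised three-group ANOVA in section 2.29.2. No baseline term is named for either randomised comparison. Yet Table 1 and section 2.21 schedule fMRI before treatment and at 12 weeks, and serum markers and scales before treatment and at 4, 8 and 12 weeks.

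The only planning figures are in section 2.5. They are improvements, that is, changes: treatment "can improve scores on the MoCA scale by 3.13 ± 0.75 and 1.53 ± 0.33 points, respectively".

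**The concern.** There are two separate issues.

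**Precision.** The trial randomises "15 participants per group". At that size, a pre-treatment value that predicts the outcome is worth using. The plan collects it for every outcome but does not name it in the arm comparison. If the t test is run on week-12 values, the baseline plays no part in that comparison. If it is run on changes, the baseline is used, but with a fixed weight that is inefficient unless r is high.

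**The decision rule.** A paired test asks whether one arm changed. It cannot attribute the change to the added treatment. Section 2.18 gives both arms glucose control and donepezil, and section 2.9.1 admits patients 3 to 12 months after stroke. Change common to both arms is therefore plausible. A rule that follows both kinds of test, concludes a difference between arms and does not name its P leaves room to report a within-arm result as efficacy on VBM, which is a primary outcome.

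**Working it through.** **1. The plan's own figure.** Section 2.5 gives "with the significance test level set at 0.05 and the test power at 0.9" and concludes that "the required sample size was 13 subjects for each group". Two-sided testing is assumed.

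- Pooled SD = √((0.75² + 0.33²)/2) = 0.579.
- Difference = 3.13 − 1.53 = 1.60, so d = 1.60/0.579 = 2.76.
- This needs 3 per arm by the normal approximation, or 5 per arm by the t test. The stated 13 is not reproduced.
- 13 × 1.15 = 14.95 gives the stated 15 after dropout.

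The mismatch is a different matter and does not bear on this point. Below, 13 is used only as the number of completers per arm and 15 as the number randomised per arm.

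**2. Precision of the arm comparison.** With 13 per arm, two-sided α = 0.05 and 90% power, the noncentral t gives a detectable effect of 1.326 SD for a t test on week-12 values. Relative to that test, the residual variance is 2(1 − r) for change scores and 1 − r² for ANCOVA. Detectable effects are therefore 1.326 × √(2(1 − r)) and 1.326 × √(1 − r²). The documents do not give r, so the values are assumptions.

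| Assumed r | t test, week-12 values | t test, changes | ANCOVA |
|---|---|---|---|
| 0.3 | 1.33 | 1.57 | 1.26 |
| 0.5 | 1.33 | 1.33 | 1.15 |
| 0.7 | 1.33 | 1.03 | 0.95 |
| 0.9 | 1.33 | 0.59 | 0.58 |

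Against week-12 values, 15 per arm with ANCOVA is worth 15/(1 − r²) = 16, 20, 29 or 79 per arm without it.

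These ANCOVA figures ignore the cost of estimating the slope. For a normally distributed baseline, chance imbalance inflates the variance by about 1 + 1/(2 × 13 − 4) = 1.045, or about 2% on the SD scale. The one lost degree of freedom adds a little more. The ANCOVA column then becomes about 1.30, 1.18, 0.97 and 0.59. ANCOVA keeps a clear lead over changes up to r = 0.7. At r = 0.9 the two are practically equal.

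**3. What a within-arm rule would do.** Suppose both arms truly change by the same amount g, in SDs of the change, with 15 per arm. Let p be the noncentral-t power of the paired test (two-sided 0.05, uncorrected, one measure). The chance that the experimental arm is significant and the control arm is not is p(1 − p).

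| g | p | p(1 − p) |
|---|---|---|
| 0.3 | 19% | 15.5% |
| 0.5 | 44% | 24.6% |
| 0.8 | 82% | 14.7% |
| 1.0 | 95% | 4.8% |

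There is no treatment effect in any row. The proper between-arm test would err in that direction 2.5% of the time. If a significant paired test in the experimental arm alone were read as success, the false-positive rate would be p itself. These figures are for a single measure; voxel maps with cluster correction would give other values, but the logic is the same.

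**The case against.** The strongest case on the other side has four parts.

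- **The between-arm t test is valid.** Randomisation protects it and its standard error already allows for chance baseline imbalance. Both arms receive donepezil, so this test cannot mistake donepezil, practice or recovery for efficacy. A reader might infer that it can; the documents do not support that. This stands in full, and the cost is precision only.
- **The plan may intend changes.** Section 2.5 is built on improvements. A reader might infer that the plan ignores baseline and so discards most of the information for a repeatable measure such as regional brain volume. That holds only if week-12 values are tested, which is not stated. If changes are tested, little is lost at high r. This stands, and it is why both comparators are shown.
- **The rule may mean only the between-arm P.** Its conclusion is worded as a difference between arms, which the two-sample test addresses. That paired tests actually feed the decision is one literal reading, not an established fact. What remains is that the text does not exclude it.
- **MoCA-based arguments do not reach the imaging rule.** Selection on MoCA < 26 and repeated testing concern the scales. Section 2.29.1, which covers the scales, never converts a paired result into an arm difference. The control-arm gain of 1.53 ± 0.33 points in section 2.5 is a 4-week MoCA figure from earlier work. It shows that change without acupuncture-rehabilitation happens, not that the imaging rule will fail.

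A reader might also infer that repeated visits are tested one at a time. Section 2.29.1 does not say so, and section 2.28 leaves a statistical analysis plan to a third party. Modelling of visits can properly be settled there. The choice of tests in section 2.29 is, however, already stated in the protocol.

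**Conclusion.** The point holds in a limited form. The planned comparison of the randomised arms is valid but names no baseline term and leaves its input (week-12 value or change) open. ANCOVA would lower the detectable effect with 13 completers per arm from 1.33 SD to between 1.26 and 0.58 SD over r of 0.3 to 0.9 if week-12 values are tested. If changes are tested, the gain runs from substantial at r = 0.3 (1.57 to 1.26 SD) to negligible at r = 0.9. These sizes rest on assumed values of r, equal variance at both times and two-sided testing.

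The wording of the imaging rule is a defect whatever r is. As written, it permits an arm difference to be declared from an unnamed P, and a within-arm P is not excluded. If one were used, equal change in both arms could produce a one-sided pattern of significance in up to 25% of trials, the maximum of p(1 − p). The documents do not show that the sponsor intends this.

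**What to change.** - Make the baseline-adjusted between-arm contrast at week 12 the sole basis for efficacy: ANCOVA of the week-12 value on arm plus baseline.
- For voxel maps, test arm × time or adjust for the baseline map.
- For the 4, 8 and 12 week measures, a mixed model with baseline, arm, visit and arm × visit is an option, with the week-12 arm contrast as the main result.
- In section 2.29.2, state that the P in the decision rule is the between-arm P. Describe the paired within-arm tests in sections 2.29.1 and 2.29.2 as descriptive only.
- If a t test is kept, state whether it uses week-12 values or changes.

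No new data are needed. The cost is one or two degrees of freedom and some wording.
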